### Aims

The primary aim of this study is to assess the feasibility and potential efficacy of a 6-week, pilot, classroom-based, physical activity intervention (ACTI-BREAK programme) on achievement in mathematics and reading in children in years 3 and 4 (aged approximately 8 to 10 years) attending primary (elementary) school in Melbourne, Australia. The impact of ACTI-BREAK on children’s on-task classroom behaviour and objectively measured school-day physical activity levels will be explored as secondary aims.

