### Power calculation

The detectable difference, based on grade-based benchmarks for year-3 reading scores in the Wheldall Assessment of Reading Passages (WARP) test [37] at mid-year, and 12 clusters (classes) per group, each with nine students, is 23.55 points in reading achievement with power set to 80%. Based on results from this study effect sizes will be generated to inform the sample size needed for a full-scale trial.

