### Primary outcomes

The primary outcome of academic achievement will be assessed using measures of reading and mathematical achievement. These assessments were chosen as the primary outcomes for this study as these are the two key pillars by which teachers and schools assess academic progress [36].

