### Data analysis

All statistical analysis will be conducted using Stata 14.0. Multilevel mixed-effects linear regression models will be used to assess the impact of group (intervention vs. control) on achievement scores in reading and mathematics, mean per cent of time in on-task behaviour, and physical activity level at the end of the intervention, each adjusted for baseline levels of the corresponding variable and clustering by class. All analyses will control for physical activity levels at baseline. The fixed effect of school will be added to the model to account for the unit of randomisation. All analyses will be stratified by sex. Alpha levels will be set at *p* < 0.05. As this is a pilot study, the intervention will not be adequately powered to detect small changes between groups. Instead, trends in associations will be investigated. Analyses will be conducted both on the intention-to-treat approach, and per protocol analysis (using data from fidelity checks).

Process evaluation data from focus groups and interviews will be analysed using Braun and Clarke’s six phases of thematic analysis [60]. Codes will be generated, and continually revised throughout the analysis process. Following coding of the transcripts, themes will be identified and defined. These data, along with data obtained from student enjoyment and satisfaction questionnaires, will provide information that can be used to improve the programme for future testing.

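### As written, every analysis is split by sex and no overall group effect is named, although the aim, the detectable difference and the sample size all concern boys and girls together

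*Protocol article*

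**What the plan says.** The Aims section sets out to assess feasibility and potential efficacy "on achievement in mathematics and reading in children in years 3 and 4". It gives no sex-specific objective, and the Discussion restates the aim in the same general terms. Under Primary outcomes, "The primary outcome of academic achievement will be assessed using measures of reading and mathematical achievement", so there are two primary measures.

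The Power calculation section reads "The detectable difference, based on grade-based benchmarks for year-3 reading scores" and "12 clusters (classes) per group, each with nine students", giving a difference that "is 23.55 points in reading achievement with power set to 80" per cent. It adds that effect sizes from this pilot will be used to size a full-scale trial. The Study setting section builds the total of 216 children from all consenting pupils in each class.

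The Data analysis section then states: "Multilevel mixed-effects linear regression models will be used to assess the impact of group (intervention vs. control) on achievement scores in reading and mathematics". It adjusts for baseline and clustering, sets alpha at 0.05 and adds the rule "All analyses will be stratified by sex". It concedes that "the intervention will not be adequately powered to detect small changes between groups".

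**The concern.** The stratification rule has no exception, and the article names no analysis of all children. A team following the text would fit one model in boys and one in girls for each outcome. The question in the aim, whether the programme affects achievement in year-3 and year-4 children, would then have no estimate of its own.

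Three things are at stake:

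- **Main result:** it becomes two less precise answers per outcome, in a trial that already admits limited power with everyone included.
- **Detectable difference:** the published figure describes an analysis that the plan does not contain.
- **Full-scale trial:** it would be sized from an overall effect size that the plan does not produce.

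**Working it through.** **1. What stratified means here.** The same paragraph handles covariates in other words: outcomes are adjusted for baseline, analyses control for physical activity, and a school effect is added to the model. Stratified is used only for sex. Separate models for boys and girls is therefore the natural reading.

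**2. The plan's own figures.**
- Sample: 6 schools × 4 classes × 9 children = 216, or 108 per group. Nine per class follows from 0.37 × 23 = 8.5. Sex does not enter.
- Detectable difference: 23.55 cannot be reproduced, because the article gives neither the standard deviation nor the ICC. It can be inverted. With (1.960 + 0.842) × SD × √DE × √(2/108) = 23.55, where DE is the design effect, SD × √DE = 61.8. This uses all 108 children per group, so it is a pooled figure.

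**3. Precision within one sex.** Assumptions not in the documents: total variance 1, class ICC 0.10, even sex split (4.5 per class instead of 9), no baseline adjustment. With 3 schools and 12 classes per group and m children per class, the variance of the group effect is

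2 × [school ICC/3 + 0.10/12 + (0.90 − school ICC)/(12m)].

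| School ICC | Variance, m = 9 | Variance, m = 4.5 | Ratio | SE increase |
|---|---|---|---|---|
| 0 | 0.0333 | 0.0500 | 1.50 | 22% |
| 0.02 | 0.0463 | 0.0626 | 1.35 | 16% |
| 0.05 | 0.0657 | 0.0815 | 1.24 | 11% |

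**4. Power within one sex.** Take the pooled analysis to have 80% power at 23.55, as stated. Within-sex power is Φ(2.802/√ratio − 1.960). This gives Φ(0.33) = 63%, Φ(0.45) = 67% and Φ(0.56) = 71%. The difference detectable at 80% power becomes 23.55 × √ratio = 28.8, 27.4 and 26.2 points.

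**5. Sensitivity.**
- With class clustering only, the within-sex detectable difference runs from 33.3 points (ICC 0, power 51%) to 25.9 points (ICC 0.30, power 72%).
- With a 40:60 split at class ICC 0.10, the SE rises 32% in the smaller sex and 16% in the larger.

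**6. Number of primary tests.** Two outcomes × two sexes = 4 tests at 0.05, against 2 if pooled. Boys and girls share classes and schools, so their estimates are correlated. From step 3, that correlation is the school and class part of the variance divided by the whole: 0.0167/0.0500 = 0.33, 0.0300/0.0626 = 0.48 and 0.0500/0.0815 = 0.61. The chance of at least one false positive was simulated from a four-variate normal with product correlation structure:

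| Reading–mathematics correlation | Two pooled tests | Four tests at school ICC 0 / 0.02 / 0.05 |
|---|---|---|
| 0 | 9.8% | 18.0% / 17.4% / 16.7% |
| 0.5 | 9.1% | 16.8% / 16.2% / 15.5% |

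**The case against.** The strongest reply is that the rule may mean sex-specific results in addition to an overall one. The models are introduced as assessing group, and the power statement and sample size are pooled, so an overall contrast is the design's frame. That stands in part. A reader might infer that the overall effect will never be estimated, and the documents do not establish that. They establish only that no overall estimate is named and that the rule as worded leaves no room for one.

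A reader might also count the missing interaction test and the missing multiplicity rule as faults. This is a condensed article and its analysis plan is not shown. Such details are commonly left to that plan, so they are not held against it here.

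On size, three cautions hold:

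- Halving the children does not halve the information, because all 12 classes per group remain.
- Not all of the 15.5–18% comes from stratification. About 9–10% is already there from two outcomes each tested at 0.05. Treating the sexes as independent would give 1 − 0.95⁴ = 18.5%, which ignores their shared classes and schools.
- The calculation leaves out baseline adjustment and treats school as a variance component, whereas the plan adjusts for baseline and enters school as a fixed effect. The percentages are a guide to size and do not predict the planned model's output.

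Pilot status softens the consequences, since the article says it will look at trends. It does not remove the mismatch: limited power is a reason not to split the sample, and the stated use of the results calls for an overall effect size.

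**Conclusion.** The point holds as a mismatch between aim and analysis. Read plainly, the Data analysis section specifies only sex-specific models, while the aim, the detectable difference and the sample size refer to all children. The 23.55-point figure thus belongs to no planned analysis, and no overall effect size is produced for the full trial.

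The loss of precision is moderate: 11% to 22% in the standard error, with power for the stated difference between 63% and 71% instead of 80%, under the assumptions in the working. The added false-positive risk is roughly 6 to 8 percentage points and is illustrative. The mismatch itself rests on the text and needs none of these assumptions.

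A reader might go further and predict that a result significant in one sex only will be reported as a sex difference. The article plans no such claim, so that is not part of the conclusion.

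**What to change.** State that the primary analysis of each outcome is one pooled model in all children, with sex as a fixed covariate. Report sex-specific effects as exploratory estimates with confidence intervals, from a group-by-sex interaction in the same model. If an overall analysis was always intended, the same sentence makes that clear.

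The cost is about one sentence of analysis wording. No new data and no design change are needed, and the article reports that the trial is still recruiting. The only downside is that sex-specific results become exploratory.

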## Discussion

The primary aim of this study is to examine the potential efficacy of a classroom-based physical activity programme known as ACTI-BREAK on children’s achievement in mathematics and reading. The impact of ACTI-BREAK on children’s on-task behaviour and objectively measured school-day physical activity levels will be explored as secondary aims. Given that the programme is designed to be delivered by trained classroom teachers in the ‘real-world’ context, assessment of feasibility and fidelity will be a key feature of the pilot study.

A strength of this intervention is that it was developed with input and guidance from current primary school teachers to limit discrepancy between evidence and practice observed in previous studies [4]. For example, our interviews with teachers indicated that anything longer than 5 min would be unlikely to be adopted. Many existing active break programmes require active break durations of between 10 and 15 min [19, 21, 24–26]. However, longer duration active breaks may be unlikely to be feasible beyond the study setting [61].

An additional strength of this study is the use of a curriculum-based measure to assess achievement in reading and mathematics. These tools are sensitive to small changes in academic achievement, and can be administered frequently (e.g. weekly) [62, 63]. Many existing studies have had short intervention periods (less than 1 year) and used standardised tests to assess intervention effects on academic achievement [29, 30]. These tests are designed to be administered at least 1 year apart [32], and, therefore, important intervention effects on academic achievement are unlikely to be observed. The use of a curriculum-based measure in the current study provides a more suitable measure of academic achievement for the 6-week intervention period, making short-term progress in academic achievement more likely to be observed.

In addition to choice of academic outcome measure, the use of an objective measure of physical activity intensity and cluster randomised controlled trial study design are further strengths of this study. To the author’s knowledge, one previous active break intervention has used an objective measure of physical activity intensity [18]. However, that study relied on teacher reports of active break implementation in the past week (to compare physical activity levels of implementers vs. non-implementers) and intervention effects on physical activity levels were assessed on a subsample of participants only [18]. Nonetheless, results from that study highlight the potential for active breaks to contribute to increased physical activity across the school day [18].

Results from this study will provide insight into the feasibility of introducing frequent, short, moderate-intensity active breaks into classroom routines, given potential challenges in their application. Further, this study will explore whether this approach will provide enhanced benefits on academic-related outcomes, compared with breaks in sitting time.

### Limitations

Given that some of the teachers who participated in the intervention development referred to using active breaks in their classrooms previously, it is possible that some teachers in the control schools may also do active breaks in their classrooms. However, teachers in the intervention development mainly referred to ad-hoc stretches and coordinative exercises (e.g. Brain Gym); thus, any active break activities conducted by teachers in control schools are not likely to be as frequent or intense as those prescribed in the ACTI-BREAK programme. A further potential limitation relates to the use of teacher-reported observations of classroom behaviour. These observations will be recorded by the same teachers who will be delivering the intervention and thus have potential for bias. However, to the authors’ knowledge, only one previous study has used such measures which were shown to be reliable (alpha = 0.85) [18].

## Conclusions

This study has the potential to enhance key educational outcomes (e.g. reading and mathematics achievement) which may encourage teachers and school administrators to provide more opportunities for children to be active at school through incorporating short, active breaks into the classroom routine. The ACTI-BREAK programme has been designed to be a time-efficient, feasible and appealing approach to physical activity promotion in schools. This study will assess required teacher time commitment, the potential for the ACTI-BREAK programme to improve academic-related outcomes and physical activity levels, and its acceptability to teachers and students, with the potential for a full-scale efficacy trial in the future.

### Trial status

The trial is currently recruiting.
